## Trial design {8}

A 7-month randomized, cross-over, two-arm, open-label, superiority trial with a 1:1 allocation ratio to either intervention or control arms will be conducted, adhering to the SPIRIT reporting guidelines (see Fig. 1 and Supplementary file 1). In the development of the study protocol, there was no direct involvement from the public or patients. Despite the acknowledged significance of patient and public engagement in research, the protocol for this study was formulated within the framework of scientific and clinical expertise.

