### Participant timeline {13}

The study timeline is depicted in Fig. 2. Before starting the intervention, a 2-week run-in period will be implemented during which participants will be asked to complete a 3-day dietary record. Subsequently, participants will be randomly allocated into two groups: one assigned to the intervention arm and the other to the control arm. There will be four clinical evaluations of the study population: at the beginning (time 0) and at month 3 (T1) of the first dietary intervention, and at month 4 (T2) and month 7 (T3) of the second dietary intervention. At each time point, assessments of anthropometric measurements, body composition, and blood pressure will be made, and blood, stool, and urine samples will be collected.

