### Sample size {14}

Sample size calculation is based on the results of a previously published study evaluating the impact of a MD intervention on human health [19]. To detect a 10% change in LDL-cholesterol levels with a statistical power of 90% (beta) and alpha set at 0.05, a randomization of 38 subjects (≥ 19 subjects in each group) is considered necessary. Considering possible dropouts, the number of participants was increased to 25 per group. Dropouts will be incorporated into the intention-to-treat analysis, including all participants initially randomized. In addition, per-protocol analysis will be conducted, focusing on those who successfully complete the study without major deviations.

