## Statistical methods

### Statistical methods for primary and secondary outcomes {20a}

Statistical analyses will be performed using SPSS software for Macintosh (SPSS Inc., Chicago, IL, USA). A *P* value < 0.05 will be considered statistically significant. Data will be analyzed using intention-to-treat and on-treat procedures. The primary outcome (change in body weight) will be analyzed within each group using Student’s *t*-test for paired data. The difference in absolute change (mean value at baseline subtracted from the mean value after the intervention for each subject) will be estimated using the Student’s *t*-test for independent data. Evaluation of distributions and checking for outliers will be performed using histograms and box plots. If appropriate, variables will be logarithmized to normalize the distributions of data. Continuous variables that follow a normal distribution will be summarized using the mean and standard deviations. Categorical variables will be presented in terms of frequencies and percentages. After testing the regression assumption, a general linear model for repeated measurements with adjustments for possible confounding factors will be run to compare the effects of different interventions. Data for the general linear model will be reported as geometric means and 95% confidence intervals. The same analyses will be performed for secondary outcomes. Microbial alpha (richness, Simpson’s, Gini-Simpson’s, inverse Simpson and Shannon’s indices, evenness and dominance) and beta (weighted UniFrac and Bray–Curtis dissimilarity) diversity measures will be assessed using QIIME (v. 1.9).

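### The repeated-measures general linear model that compares the diets is, on its ordinary reading, a complete-case analysis, so it does not deliver the promised intention-to-treat analysis of everyone randomised

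*Protocol article*

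**What the plan says.** - **Comparison of the diets.** Statistical methods {20a} says that "a general linear model for repeated measurements with adjustments for possible confounding factors will be run to compare the effects of different interventions", and that "Statistical analyses will be performed using SPSS software for Macintosh". No SPSS procedure, data layout or repeated factor is named. The same section also compares each participant's change between the diets with a t-test for independent data.
- **Analysis population.** Sample size {14} says: "Dropouts will be incorporated into the intention-to-treat analysis, including all participants initially randomized". A per-protocol analysis of those who finish without major deviations is listed separately.
- **Visits.** Participant timeline {13}: "There will be four clinical evaluations of the study population", at time 0, month 3 (T1), month 4 (T2) and month 7 (T3).
- **After discontinuation.** Section {18b} states that participants who stop early have no further clinical or laboratory evaluations.
- **Missing data.** Section {20c} plans sensitivity analyses that give missing outcomes best or worst values. Multiple imputation under random missingness follows only if those analyses could change the conclusions.
- **Numbers.** Sample size {14}: "a randomization of 38 subjects (≥ 19 subjects in each group) is considered necessary", and then, for possible dropouts, "the number of participants was increased to 25 per group".

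**The concern.** A classical repeated-measures general linear model takes one row per participant and needs every repeated cell filled. A participant who completes the first diet and then leaves is deleted whole, including the LDL values already measured at time 0 and T1. Because evaluations end at discontinuation, such incomplete rows are to be expected.

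The model would then describe completers, whom the protocol treats as a separate per-protocol population, while being reported under an intention-to-treat label. The t-test of changes would keep a lone first-period change. The two planned between-diet comparisons would therefore run on different people, with nothing to say how a disagreement between them is read.

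At stake are agreement with the stated analysis population and some precision. If leaving depends on the LDL response to the first diet and differs between sequences, the diet contrast is also biased. Participants are not blinded, so unequal leaving by diet is possible, although the protocol gives no evidence for it.

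**Working it through.** **1. The plan's own figure.** Sample size {14} aims "To detect a 10% change in LDL-cholesterol levels with a statistical power of 90% (beta) and alpha set at 0.05". It gives no SD, so 38 cannot be reproduced. Solved backwards (two-sided), 19 per group implies a standardised effect of (1.960 + 1.282) × √(2/19) = 1.05. Read as a paired design with N = 38, it implies 3.242/√38 = 0.53.

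**2. Dropout margin.** 50 − 38 = 12, and 12/50 = 24%. The protocol states neither this rate nor this count. If 12 are deleted, 38 remain, which is the planned number. On the two-group reading, power is 90.0% with 19 per group and 96.1% with 25.

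**3. Assumptions for the rest (none is in the documents).** Between-person SD 25 mg/dL, visit-to-visit SD 12, diet effect 13, a random-intercept model with fixed visit effects, and no carry-over.

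**4. Precision.** In this model, complete participants inform the diet effect through the T1-minus-T3 contrast:
- 38 completers: SE = ½ × 12√2 × √(2/19) = 2.753.
- 38 completers plus 12 partial records, dropout spread evenly over T1, T2 and T3: SE = 2.667. Variance ratio (2.753/2.667)² = 1.07.
- 38 completers plus 12 who leave after T1: SE = 2.640. Ratio (2.753/2.640)² = 1.09.

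Discarding the partial records of dropouts therefore costs about 7–9% in variance.

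If 12 people miss only T2, the SE on all observed visits is 2.400, a ratio of 1.32. That equals ½ × 12√2 × √(2/25), the value for 50 complete participants, because T2 carries no information on the diet effect in this model. The 32% is simply 50/38. It should not be offered as the cost of dropout, particularly as Outcomes {12} defines the metric as change within each diet period, for which T2 is the second baseline.

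**5. Bias.** Simulated trials with 12 leavers after T1, being those with the largest first-period LDL rise within their sequence. Bias is in mg/dL, and leavers are counted as high-UPF-first versus low-UPF-first:

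| Leavers | Complete-case, difference of changes | Complete-case, same model as the last column | All observed visits |
|---|---|---|---|
| 12 v 0 | about -6.2 | about -3.1 | about 0 |
| 8 v 4 | about -2 | about -1 | about 0 |
| 6 v 6 | about 0 | about 0 | about 0 |

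The first and last columns differ in both estimator and data set. The second and last differ only in who is included, so they isolate the effect of deletion: with 12 versus 0, about 3.1/13 = 24% of the assumed effect. Under the same assumptions, the t-test on all available changes is also essentially unbiased (-0.04, -0.08 and -0.10 in the three rows).

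**The case against.** The strongest objection is that deletion is inferred. SPSS also offers mixed models, and an article may leave the choice of procedure to a fuller document. This stands in part. Deletion is the ordinary consequence of the named model class but is not documented, and a few words could show that a likelihood-based model was meant. Against that, the article does fix both a model and a population, and on the usual meaning the two do not fit.

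A second objection is that nothing ranks this model as the primary analysis: the t-tests are listed first. That is right, so the point concerns this model and not every planned comparison.

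Four stronger readings are tempting, and the documents do not support them:
- *Dropouts are never analysed.* Section {20c} gives them best and worst values and may impute them, and the t-test keeps a completed first period. What is missing is a place for them in the main run of this model.
- *The plan expects 12 non-completers.* Twelve is only the difference between 50 and 38.
- *Deletion biases the result by half the effect.* That needs all 12 leavers to come from one sequence and to be exactly those with the largest rises, and it mixes a change of estimator with a change of data set.
- *Power falls below plan.* Deletion to 38 leaves the planned size.

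**Conclusion.** The point holds in a limited form. On its ordinary reading, the model that compares the diets omits anyone without all four visits. The intention-to-treat analysis promised in Sample size {14} is then not delivered by that model, and section {20c} supplies only sensitivity analyses and conditional imputation. The two between-diet comparisons would also use different participants.

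The size is modest. For 12 leavers, the loss is about 7–9% in variance. Bias is near zero with balanced dropout, about -1 to -2 mg/dL with 8 versus 4 leavers, and -3 to -6 mg/dL, depending on the estimator, only at the 12 versus 0 extreme. These figures rest on the assumed SDs, effect and dropout mechanism. The mismatch between model and population does not depend on them. The change should be made, but the trial's planned size is not in question.

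**What to change.** In Statistical methods {20a}, replace the repeated-measures general linear model with a linear mixed model (SPSS MIXED) on all observed LDL values from T0 to T3. Use a participant random effect and fixed effects for visit/period and diet, and include every randomised participant with at least one value. Name it as the intention-to-treat analysis of Sample size {14}, and keep those who complete without major deviations as the per-protocol analysis. If a mixed model was intended all along, naming the procedure settles the point.

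The cost is a change of wording: same software, no new data. The small downside is that the model assumes missingness depends only on observed data, which section {20c} already assumes for its imputation. The best/worst-case analyses can stay as the check on that assumption.

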### Interim analyses {21b}

No interim analysis will be conducted.

### Methods for additional analyses (e.g., subgroup analyses) {20b}

Subgroup analyses will be performed to analyze possible differences in the changes, according to specific characteristics of the study population (age and sex).

### Methods in analysis to handle protocol non-adherence and any statistical methods to handle missing data {20c}

Before starting the data analysis, the level and possible causes of missing data will be investigated using appropriate tables. This information will be used to determine whether the level and type of missing data have the potential to introduce bias into analysis results or substantially reduce the precision of the estimates for the proposed statistical methods. Sensitivity analyses will be performed, based on the assumption that the missing outcomes are the worst or best possible in the different randomization groups. If these show that the conclusions may differ based on the missing values, further multiple imputation will be performed for the missing values. These analyses will consider the results of any losses at follow-up to the extent that they relate to differences in the measured variables (i.e., under the assumption of random missingness).

### Plans to give access to the full protocol, participant-level data, and statistical code {31c}

The datasets analyzed during the current study and statistical code are available from the corresponding author on reasonable request, as is the full protocol.

## Oversight and monitoring

### Composition of the coordinating center and trial steering committee {5d}

Regular monitoring of this study will be conducted by both the research team and the local Institutional Review Board. Given the study’s limited objectives, short duration, and the low-risk nature of the intervention, the establishment of a data monitoring committee and a trial steering committee was deemed unnecessary. A management board, chaired by the principal investigator (PI) and including one representative from each RU, will monitor the progress of activities toward the targets. The board will meet at least every 6 months and whenever needed depending on the progress of scientific activities, with detailed reports about the findings and discussions on the putative critical points. The board will be in charge of the definition of the deadlines related to the different steps of the project as well as to the relative reports, to be shared with all the consortium participants. Finally, annual reports on activities and financial matters will be prepared.

### Composition of the data monitoring committee, its role and reporting structure {21a}

The research group, appointed by the principal investigator, comprises additional two study coordinators, two physicians, six nutritionists, and two biostatisticians.

### Adverse event reporting and harms {22}

Adverse events, such as unfavorable and undesirable signs, symptoms, abnormal laboratory results, or illnesses temporally associated with the intervention diet, will be collected from the time of randomization until the final 7-month follow-up visit for each participant, whether or not they are considered related to the intervention study. All adverse events will be followed up until their resolution.

### Frequency and plans for auditing trial conduct {23}

The team will convene regularly, typically monthly, to comprehensively assess ongoing trial progress. This includes a thorough review of study advancements, recruitment rates (actual versus predicted), data quality and return rates, protocol amendments, and general research study matters. The principal investigator will oversee these meetings, developing the agenda and serving as the study’s primary contact. At the halfway point and conclusion of the study, the protocol team will furnish the local Institutional Review Board with a comprehensive monitoring report, encompassing a review of activities, progress, challenges, and any pertinent issues of concern.

### Plans for communicating important protocol amendments to relevant parties (e.g., trial participants, ethical committees) {25}

Any changes to the protocol and information provided to participants will be submitted to the Ethics Committee for approval prior to implementation.

## Dissemination plans {31a}

The study results will be shared through several channels. Investigators will present findings at both national and international scientific conferences, and a dedicated webinar for Italian nutritionists will elucidate UPF consumption within the MD. Scientific publications in peer-reviewed journals are part of the dissemination plan. The strategy encompasses public involvement, featuring a consumer event, participation in “Researchers’ Night,” and the creation of informative materials. An online and social media campaign will enhance visibility, engaging a wide audience, including stakeholders and the public.

## Discussion

The scientific literature on UPF reports divergent perspectives, mainly revolving around the interpretation of observational data and the need for rigorous interventional studies. Advocates for public health policies restricting UPF intake and incorporating UPF guidelines into dietary recommendations rely on epidemiological evidence linking their consumption to adverse health outcomes [34–36]. In contrast, part of the scientific community calls for a cautious interpretation, citing the inherent limitations of observational studies and the need for randomized controlled trials to establish causality and clarify underlying mechanisms [37–39]. Furthermore, there is acknowledgment of the heterogeneity within UPF, with recent data suggesting that not all UPF pose equal health risks [40, 41].

In this context, the PROMENADE study represents a pioneering effort as the first clinical trial investigating UPF consumption within the framework of a MD. Its potential impact extends across scientific, industrial, and social dimensions, serving as a significant contribution to the ongoing discourse on nutrition, health, and sustainability. Scientifically, PROMENADE is expected to contribute to our understanding of the relationship between food processing and health in the context of a dietary intervention based on the MD. The results have the potential to provide insights into the degree to which food processing, particularly UPF, influences the impact of the MD on human health. From an industrial perspective, insights from the study may guide the formulation of UPF with improved nutritional profiles, aligning convenience with health considerations within a sustainable food model. At a social level, dissemination of results could enhance informed dietary choices on a broader scale.

Beyond its implications for human health, PROMENADE also holds relevance for planetary health. UPF consumption is associated with unsustainable agricultural practices and excessive packaging waste, contributing to environmental degradation [42–44]. In contrast, the MD aligns more closely with sustainable food production practices, boasting a lower environmental footprint [4]. By examining the combined effects of UPF consumption and adherence to a Mediterranean-based dietary pattern on both human health and the environment, the trial can inform dietary recommendations that promote individual health while minimizing the ecological impact of food production.

Strengths of the study include its randomized controlled trial design, enabling rigorous assessment of causal relationships. Randomization minimizes confounding factors, enhancing internal validity and allowing for more reliable conclusions. Additionally, comprehensive outcome measures, including body weight and composition, metabolic markers, and gut microbiota composition, provide a holistic understanding of the potential impacts of dietary interventions. Main limitations include study duration and sample size, which may challenge generalizability, and reliance on self-reported data that introduces the possibility of recall bias. Nevertheless, despite these limitations, the PROMENADE study holds promise in advancing our understanding of the impact of UPF consumption on both human and planetary health. By contributing substantively to the ongoing scientific discourse on this critical topic, it has the potential to inform future research endeavors and public health initiatives.

## Trial status

The study has received all necessary regulatory approvals. The currently approved version of the protocol is 2.0 (version date 21/11/2023). Recruitment will begin in April 2024 and the completion date is scheduled for April 2025.

## Data Availability

Access to the final trial dataset will be restricted to the research team to ensure confidentiality and privacy protection for participants. The principal investigator will be responsible for safeguarding participants’ privacy, and data, along with source documents, will be stored securely for potential monitoring or inspection by the Ethics Committee. Upon completion of the study, participants have the option to request a copy of the study results from the principal investigator, promoting transparency and participant engagement. The final report will adhere to the CONSORT 2010 guidelines, ensuring comprehensive reporting standards. To contribute to the scientific community’s knowledge, study results will be submitted for publication in a peer-reviewed journal. Additionally, plans for dissemination at national and international conferences will be collaboratively discussed with researchers before implementation, promoting widespread sharing of findings.

## Abbreviations

BMI: Body mass index
DNA: Deoxyribonucleic acid
ELISA: Enzyme-linked immunosorbent assay
FA: Fatty acid
GC-MS: Gas chromatography-mass spectrometry
H2O2: Hydrogen peroxide
HOMA-IR: Homeostatic Model Assessment for Insulin Resistance
HPLC–MS/MS: High-performance liquid chromatography-tandem mass spectrometry
ICMJE: International Committee of Medical Journal editors
IL: Interleukin
LDL: Low-density lipoprotein
LPS: Lipopolysaccharides
MD: Mediterranean diet
MFW: Metabolic Food Waste indicator
NaOH: Sodium hydroxide
NFFQ: NOVA Food Frequency questionnaire
PAI-1: Plasminogen activator inhibitor 1
PI: Principal investigator
rRNA: Ribosomal ribonucleic acid
RBC: Red blood cell
RU: Research unit
SCFA: Short-chain fatty acids
SPIRIT: Standard Protocol Items: Recommendations for Interventional Trials
TGF-β: Transforming growth factor-β
TNFα: Tumor necrosis factor-alpha
UPF: Ultra-processed foods
